| **Methods**  **Study outcomes –** The primary outcome will be the proportion of subjects developed GDM at 24-28 weeks gestation in in both groups as measured using a 75 g 2-h oral glucose tolerance test (OGTT). The secondary outcomes will include the proportion of neonates born with LGA (>=95th percentile of the customized birth weight) and macrosomia (>=4 kg at birth) in both groups. The secondary outcomes are chosen since infants born with larger size, in particular those born with GDM mothers were associated with higher future metabolic risk as compared to those born appropriate-for-gestational age with non-GDM or GDM mothers (19).  **Sample size calculation** – Sample size was calculated based on the primary outcome, i.e. the proportion of subjects developed GDM at 24-28 weeks of gestation between the two study groups. A previous lifestyle intervention trial in obese pregnant women showed that 6% subjects developed GDM in the intervention group compared to 29% in control group (p<0.05) (20). Based on these figures, the sample size estimates for a two-sided test will be 42 per group with power of 80% at a 5% significance level to detect an 83% reduction in the odds of decreased GDM in the intervention group when compared to the control group (20). However, a more conservative sample size estimate is used as the proposed lifestyle modification program (LMP) has been modified with less frequent dietetic sessions compared with that used in our previous publications. Therefore, a sample size of 73 per group with power of 90% at a 1% significance and two-sided test will be used. Assuming 30% lost to follow-up rate and 5% miscarriage rate, a final sample size of 110 subjects per group will be required.  **Trial procedures** – Eligible subjects will be randomized in 1:1 ratio to participate in the LMP or receive usual care from the time of recruitment (i.e. <= 12 weeks gestaion) till 24 weeks gestation. Randomization will be performed through the use of a computer-generated list of random numbers in blocks of 6 by a study coordinator. Treatment assignments will be concealed in consecutively-numbered sealed envelopes, which will be opened sequentially upon subject enrollment. The interventionists (the dietitian and the exercise instructor), the subjects and the study coordinator will not be blinded to the treatment assignment. However, the interventionists will not take outcome measurements. Subjects will be reminded not to reveal information about their intervention to the outcome assessors, clinicians and nurses of routine antenatal and postnatal care. All investigators, outcome assessors, clinicians and nurses of routine antenatal and postnatal care will be blinded to the treatment assignment.  Data will be collected by trained research staff at six time points, namely <=12 weeks gestation (baseline/T0), 16-20 weeks gestation (T1), 24-28 weeks gestation (T2), 35-37 weeks gestation (T3), within 48 hours of delivery (T4), and 6-8 weeks postpartum (T5). These time points are scheduled mostly together with the routine AN care visits to minimize subjects’ burden for extra visits for the study. A cash of HK$50 per visit will be payable to each subject at T1, T2, T3 and T5.  **Intervention group** – In addition to receive routine antenatal care, subjects randomized to the intervention group will participate in a dietitian-led LMP from the first AN booking (i.e. <=12 weeks gestation) to 24 weeks gestation. The original LMP is based on a strategy of increasing energy expenditure and reducing caloric intake using lifestyle behavioral change to achieve long-lasting impact. It generally requires participants to attend dietary consultation sessions weekly in the first 3-4 months, and monthly in the subsequent months, and to see an exercise instructor at least once during the program. However, considering that frequent visits may be a burden for pregnant women but frequent contacts in early stage of pregnancy are important for effective lifestyle intervention (21); the original LMP will be modified in several aspects. Firstly, consultations will be scheduled bi-weekly instead of weekly in the first 2 months of the program and monthly to the end of the program (i.e. 24 weeks gestation). Secondly, some original face-to-face consultations in the first two months will be replaced by telephone consultations since the effectiveness of high-frequency (i.e. weekly) telephone contact with a dietitian was comparable to high-frequency face-to-face lifestyle counseling in supporting obese patients trying to lose weight (21). Thirdly, the consultation sessions will be mostly scheduled on the same day of the routine AN visits of the subjects.  At the first session (about 1 hour), the dietitian will carry out a complete behavioral assessment, covering important areas such as the subject’s pre-pregnant and current weight status, eating and lifestyle patterns, specific eating-related behaviors, traditional food taboos in pregnancy, knowledge of risks associated with current eating patterns, and concerns and feelings about specific lifestyle changes. The dietitian will review the subject’s medical, pregnant and birth history, and the weight gain in previous pregnancy. Moreover, the dietitian will review the fetal growth and the subject’s weight gain of current pregnancy, and discuss the specific dietary and lifestyle advices to achieve a desirable weight status with the subjects.  In the follow-up consultation sessions (about 20 minutes), the dietitian will review the subject’s dietary and lifestyle practices and provide recommendations. Each subject will be given an individualized menu plan aiming at achieving a varied balanced diet and a desirable fetal growth and maternal weight throughout pregnancy. The dietary component of the menu plan will be based on the American Dietetic Association’s recommendations (22). A varied balanced diet with an emphasis on fruit and vegetables, and moderate-carbohydrate, low-fat, low-GI and low-calorific products in appropriate portions will be encouraged. Each subject will be provided with two booklets, one for food portion size exchange and tips for eating out, and another listing the low-GI food options and meal plans (GI <55). Moreover, advice on use of dietary supplements and managing food cravings, nausea, vomiting and constipation will be given. Techniques for coping at-risk situations such as parties and festival celebrations will be taught. Recipes will be provided to the subjects to encourage healthy cooking. The dietitian will also encourage the subjects to send their enquiries to the dietitian by emails.  Besides, subjects will be encouraged to see an exercise instructor at least once during the LMP, which will be tried to schedule on the same day as the dietitian appointment and/or AN visits for subjects’ convenience. The exercise instructor will arrange individualized follow-up session based on his/her clinical judgment. Subjects will be encouraged to request for exercise consultations as often as they feel necessary. Ongoing support from the exercise instructor will also be available by phone calls or emails. During the exercise consultation (about 30 minutes), the exercise instructor will review subject’s medical history as well as pre-pregnant and current exercise habits, and assess subject’s fitness level and musculoskeletal problems. The exercise instructor will design a suitable exercise regime for the subject. Medical clearance is recommended for women who have been sedentary before pregnancy or who have a medical condition. The exercise instructor will use the PARmed-X for Pregnancy as a guideline for health screening for the subjects prior to participation in a prenatal fitness class or other exercise, and use the information as a reference to decide the individualized exercise prescription and the program safety. During the first trimester, pregnant women who were previously exercising may continue but modify the exercise regime in accordance with general physiological changes, like high to low impact exercise, while inactive women should refrain from exercise until the second trimester. After the first trimester, subjects will generally be advised to do a 30-minute of easy to moderate intensity of low impact aerobic exercise, including brisk walking, stationary bike, swimming or walking in water for at least three times a week. Subjects will be asked to work out at a manageable intensity which talking could be done without difficulty and with slightly elevated heart rate and breathing rate. For easy indication, the exercise instructor will ask the subjects to weigh their rate of exertion by using the 10-point Borg scale and level 1-4 indicates the exercise intensity as easy to somewhat hard. The exercise instructor will demonstrate techniques for static stretching (avoiding muscle pain) of most muscle groups (upper and lower limbs, neck and trunk muscles) to the subjects. Moreover, the exercise instructor will show to the subjects how to do resistance training, covering the major muscle groups of the arms, abdomen and legs to promote good posture, prevent low back pain and lower limb join problems. Subjects will receive written exercise prescription with frequency and duration targets, and brochures including examples for adequate exercise. Information regarding precautions of participation in a prenatal fitness class or other exercise, such as supine position over 16 weeks, overheating, breath holding and long standing will be provided to the subjects. Information regarding warning signs, such as excessive shortness of breath, dizziness and fainting to terminate exercise and when medical advice should be sought will also be provided.  To check the adherence to both diet and exercise intervention, 3-day dietary records, daily activity log sheets, pedometer readings and attendance data will be used. Participants’ adherence to both the diet and exercise intervention will be assessed by a check-list and an adherence score to each of the diet component and the exercise component will be generated. 1 score will be given for meeting each of the key recommendations given by the dietitian or the exercise instructor. Higher score indicates the participant being more adherent to the LMP.  For the diet adherence score, 1 score will be given for meeting each of the criteria below: (i) total energy not exceeding 10% of the diet plan; (ii) % energy from fat 20-30%; (iii) % energy from protein within the range of 15-20%; (iv) % energy from carbohydrate 50-60%; (v) consumption of fruit > 160g; (vi) consumption of vegetables > 240g (equivalent to 1-2 servings of fruits and 3-4 servings of vegetables); (vii) regular meal consumption as prescribed by dietitian and (viii) “Avoid food (e.g. high fat or high sugar foods/glycaemic index foods)” not being consumed. The scores will be summed up to give a dietary adherence score, ranging from 0 to 8 and a maximum of 24 scores (8 scores x 3 day) for each follow-up time point. Adherence to dietary intervention will also be assessed by calculating the percentage attendance to the intervention sessions.  Regarding the physical activity adherence, the score will be assessed based on the IPAQ-C data. Two scores will be given if 80% of the recommended volume of exercise (frequency x duration) was met during the week of follow up (7 days) while one score will be given if 50% of the recommended volume of exercise was achieved. Zero score will be given for those who did not perform any easy to moderate intensity of low impact aerobic exercise. Number of exercise consultation sessions attended by the subjects will also be documented.  To measure physical activity level more objectively, we will also use pedometers as an objective measurement to tally steps taken by the participants. However, due to limited funding budget, only a sub-group (25%) of subjects in each arm, who will be randomly chosen and will be given a pedometer to record daily step counts for up to seven consecutive days at various time points. The pedometer readings will be filled daily for 7 days at each time point.  **Control group** - Subjects in the control group will receive routine antenatal care shared between the Li Ka Shing outpatient clinic of the PWH and the Maternal and Child Health centres. The subjects will be provided with an educational pamphlet on diet and exercise during pregnancy and offered optional antenatal classes which subjected to quotas availability. An updated protocol has been implemented in the PWH since 1st May 2014 to standardize the screening, diagnosis and management of GDM.  **Measurements –** Various maternal and fetal/neonatal data will be collected using standardized methods and questionnaires, and retrieved from the hospital record.   - **Maternal physical examination measurements:** Weight, height, blood pressure and heart rate will be measured using standardized methods, and pre-pregnancy weight will be self-reported. The total gestational weight gain will be calculated as the difference in the weight measured on the day of delivery and self-reported pre-pregnancy weight. - **Maternal Laboratory assessments:** A 75 g 2-h OGTT will be done at 24-28 weeks gestation on routine AN care basis. GDM will be diagnosed using the modified WHO criteria. In the study hospital, a new protocol of diagnosis of GDM has been implemented since 1st May 2014. Only the fasting plasma glucose (FPG) and 2-h plasma glucose (PG) results of the OGTT instead of the fasting, 1-h and 2-h PG results will be used as diagnostic criteria for GDM due to resource constraints. Therefore, the primary outcome (i.e. GDM) will be diagnosed between 24-28 weeks of gestation if one or more of the following criteria are met: (i) FPG 5.1-6.9 mmol/L; (ii) 2-hour PG 8.5-11.0 mmol/L following a 75g oral glucose load. Extra OGTT will be repeated at 6-8 weeks postpartum for those who have abnormal OGTT results at 24-28 weeks gestation. - **Demographic and other lifestyle habits**, such as mother’s age, occupation, family income, smoking status and alcohol use will be collected using a standardized questionnaire at baseline. Smoking status and alcohol use will be asked again at 35-37 week gestation to check for any changes in these habits during pregnancy. - **Medical history, past/current obstetric history, medication use** will be retrieved from the hospital record and collected using a questionnaire at baseline and at 35-37 weeks gestation. - **Dietary intakes, physical activity level and use of supplements** will be assessed. A 3-day diet record including one weekend day and two weekdays will be used to assess subject’s diet. Daily nutrient intake and consumption of food group of all subjects at various time points will be calculated using the nutrition analysis software Food Processor Nutrition analysis and Fitness software version 8.0 (ESHA Research, Salem, USA) including local foods selected from food composition tables from China and Hong Kong. Since there has been no validated Chinese questionnaire for measuring physical activity level for pregnant women, the present study will use a Chinese version of the International Physical Activity Questionnaire (IPAQ-C) which has been validated among general Chinese population (23). Moreover, a general physical activity questionnaire capturing special physical activity patterns of pregnant women will be asked. A sub-group (25%, n=28) of subjects in each arm, who will be randomly chosen and be be given a pedometer (Yamax brand) to record daily step counts for up to seven consecutive days at various time points. The pedometer readings will be filled daily for 7 days at each time point. Data on use of supplements will be collected by asking subjects to specify the brand, the frequency, and the dosage of supplements used. - **Perceived support from the dietitian and the exercise instructor** will be assessed at 24-28 weeks of gestation (T2) using the Health Care Climate Questionnaire (HCCQ), a 15-item patient-rated measures on a scale of 1 (strongly disagree) to 7 (strongly agree) related to their perceived supportiveness of health care providers. HCCQ is validated among various settings. The Chinese version was validated with high internal reliability (0.93) (24). - **Perinatal and obstetric outcomes, neonatal outcomes and complications** will be retrieved from the hospital record. Perinatal and obstetric outcomes and complications will include GDM as measured by OGTT at 24-28 weeks gestation, preeclampsia, gestational hypertension, Caesarean section and preterm delivery, and gestation at delivery (week). Fetal and neonatal outcomes will include fetal ultrasound, Apgar score at 1 minute and 5 minutes, neonatal weight and length, head circumference, LGA, macrosomia and shoulder dystocia. |

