|  |
| **Data processing and analysis**  Data will be presented as mean (standard deviation), median (inter-quartile range) for skewed variables and frequency (percentage) as appropriate. Skewed variables will be corrected by necessary transformations before statistical analyses. Between-groups comparisons at baseline and after intervention will be made using the Student’s t test, Chi-square test or Fisher’s exact test, as appropriate. Multilevel models will be used to compare differences between the 2 groups for all measured outcomes including GDM prevalence, proportion of infants born LGA and macrosomia, anthropometric measures and other obstetric maternal outcomes and fetal and neonatal outcomes at baseline and 24-28 weeks gestation or at delivery with adjustment for age and other covariates. Multilevel model can be used to analyse both longitudinal continuous and discrete data (25). All statistical tests are two-sided and a p-value <0.05 is considered statistically significant. SPSS for Windows software (version 24.0, SPSS Inc., Chicago, IL, USA) will be used for the statistics. |

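### For continuous outcomes with a baseline value, the plan sets an unadjusted follow-up t test beside a multilevel model without saying which decides; one baseline-adjusted analysis should (minor)

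*Protocol*

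**What the plan says.** Under Data processing and analysis in section 3, the protocol gives two methods in consecutive sentences.

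- Simple tests: "Between-groups comparisons at baseline and after intervention will be made using the" t test for continuous variables and the chi-square or Fisher test for categorical ones. No baseline term enters these tests, and no outcome is named.
- A model: "Multilevel models will be used to compare differences between the 2 groups for all measured outcomes". The list that follows includes GDM, LGA and macrosomia, and then "anthropometric measures and other obstetric maternal outcomes". The comparison is made "at baseline and 24-28 weeks gestation or at delivery with adjustment for age and other covariates". The T0 value of the outcome is not listed as a covariate, though baseline is one of the model's time points. The protocol adds that a "Multilevel model can be used to analyse both longitudinal continuous and discrete data".

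All tests are two-sided at 0.05. The protocol does not say which method decides when both apply to one outcome. Under Measurements, it defines total gestational weight gain as day-of-delivery weight minus self-reported pre-pregnancy weight.

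**The concern.** Weight, blood pressure, heart rate, nutrient intake and activity are continuous, and T0 is a data collection point. Each such outcome can therefore receive two p-values, one from a test that ignores T0 and one from a model that uses it. The two can disagree, and with no stated order the reader cannot tell which result the trial stands on.

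The t test also leaves in its error term all the variation between women that was already present at T0. Avoiding excessive weight gain is part of the study rationale in section 1, and diet and activity are what the programme sets out to change. These outcomes would help explain a positive or a null GDM result, so they should be estimated as precisely as the collected data allow.

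**Working it through.** **Inputs from the protocol.** Two-sided 0.05; 1:1 allocation; 73 per group before inflation for losses. The inflation reproduces: 73/(0.70 × 0.95) = 109.8, hence 110 per group, and 110 × 0.70 × 0.95 = 73.2 evaluable. The protocol gives no power, SD, target difference or correlation for any continuous outcome, so there is no stated figure to reproduce there.

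**Assumptions.** For weight: SD 10 kg at both times and a true difference of 2 kg. r is the correlation between T0 and follow-up, and is varied.

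**Variance of the arm difference relative to the follow-up t test (1.00), equal SDs at both times.**

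- Difference of changes: (σ² + σ² − 2rσ²)/σ² = 2(1 − r)
- Baseline-adjusted: 1 − r²

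| r | t test | difference of changes | baseline-adjusted |
|---|---|---|---|
| 0.3 | 1.00 | 1.40 | 0.91 |
| 0.5 | 1.00 | 1.00 | 0.75 |
| 0.7 | 1.00 | 0.60 | 0.51 |
| 0.90 | 1.00 | 0.20 | 0.19 |
| 0.95 | 1.00 | 0.10 | 0.10 |

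The two right-hand columns nearly meet at high r. Below r = 0.5 the difference of changes is worse than the plain t test. Baseline adjustment is never worse than either.

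**Power for weight.** Power = Φ(2/SE − 1.96).

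- t test: SE = 10 × √(2/73) = 1.66 kg; power 23%.
- Adjusted, r = 0.7: SE = 1.66 × √0.51 = 1.18 kg; power 39%.
- Adjusted, r = 0.90: SE = 1.66 × √0.19 = 0.72 kg; power 79%.
- Adjusted, r = 0.95: SE = 1.66 × √0.0975 = 0.52 kg; power 97%.
- Difference of changes: 77% at r = 0.90 and 97% at r = 0.95.

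**Sensitivity.** Over SD 8-12 kg and true differences of 1.5-3 kg, the t test has 11% to 62% power, and the adjusted analysis at r = 0.9 has 41% to 99.9%.

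**Check of the model.** In 200 simulated trials at r = 0.95, power was 97% for ANCOVA, 97% for the group-by-time term of a mixed model with two time points, and 97.5% for that model with a common baseline mean. The t test gave 16% in these runs. The Monte Carlo standard error is about √(0.226 × 0.774/200) = 3 points, so the formula value of 23% is the one used here.

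**The case against.** The strongest reply is that the planned model already does the work. It includes baseline as a time point and names anthropometric measures, and at r = 0.95 its group-by-time contrast equals the proposed analysis (0.10 v 0.10). The t-test sentence is generic and does not prescribe a t test on raw weight. Total gestational weight gain is already a change score. The model's exact terms may properly sit in an SAP that is not to hand. All of this stands, and it limits the point.

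A reader might infer more than the text supports:

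- That the baseline value is wasted, or that a real weight difference will be declared null. This holds for the t test alone, not for the model planned in the next sentence.
- That omitting T1 and T3 from the model costs power for weight. The protocol does not say that weight is measured at those visits, T3 falls well after the programme ends at 24 weeks, and the simulation recovers the gain without them.
- That the width of the visit windows matters. Even an assumed 0.45 kg per week over 4 weeks adds 0.45 × 4/√12 = 0.52 kg of SD, taking 10 kg to 10.01 kg.
- That the baseline tests distort the result. They alter no treatment comparison.
- That the model uses a separate baseline mean per arm. The protocol does not say so; the difference-of-changes column is one reading of an open text.

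What the reply does not answer is that both methods are stated for the same outcomes at the same threshold with no order between them, and that one of them ignores T0.

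**Conclusion.** The point holds in a limited form and is minor. For continuous outcomes with a T0 value, the protocol states two competing inferential analyses and does not say which decides. The t test is inefficient where T0 predicts follow-up well: 23% power for weight against 79-97% adjusted at r = 0.90-0.95. The model, if it is a difference of changes, is as good as adjustment for weight but loses precision where the correlation is moderate or low, as may be so for blood pressure or diet records (1.00 v 0.75 at r = 0.5; 1.40 v 0.91 at r = 0.3).

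These sizes rest on an assumed SD, difference and correlations. The ordering 1 − r² ≤ 1 and 1 − r² ≤ 2(1 − r) does not depend on the particular r, given equal SDs at both times. GDM, LGA and macrosomia are binary with no T0 value and are untouched. Only tertiary and process outcomes are affected.

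**What to change.** For continuous outcomes with a T0 value, remove the post-intervention t test as an inferential test and name one baseline-adjusted analysis as the deciding one. This can be ANCOVA with T0 as covariate, or the planned multilevel model with a common baseline mean for both arms. Define the treatment effect as the arm difference at 24-28 weeks, or at delivery where that is the outcome's time point. Keep simple tests for outcomes with no T0 value, such as birth weight, and keep total gestational weight gain as defined. If an SAP exists, the two documents should agree on this.

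The cost is rewording two sentences and slightly more modelling. No new data are needed beyond the T0 values, and multilevel modelling is already planned.
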